**Studyprocedures**								
Vital signs including SpO2	X	X	Daily until discharge					
Clinical data collection	X	X	Daily until discharge				X	
Targeted medication review	X	X	Daily until discharge				X	
Adverse event evaluation	X	X	Daily until discharge				X	
ECG^b^	X	X	QT monitoring scheme					
Evaluation by telephone					X	X	If outpatient visit is not feasible	x
Evaluation on outpatient clinic							X^a^	
Spirometry + reversibility							X^a^	
Lung volumes + diffusion							X^a^	
Low-dose CT scan							X^a^	
6-min walking distance							X^a^	

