**Laboratory**								
CRP, hematology, chemistry, kidney and liver test	X	At clinician’s discretion	At clinician’s discretion				X^a^	
Pregnancy test for females of childbearing potential	X							
Viral qPCR (nasopharyngeal swab)				If feasible				

^a^If clinically feasible

^b^QT monitoring scheme: Long QT (> 470 ms males and > 480 females) is an exclusion for participation. In patients with no long QT on ECG but at risk, a QT monitoring will be performed with intermittent ECG monitoring at days 2–3 or continuous follow-up on ICUs. When QTc > 500 ms and/or delta QTc > 60 ms, IMP will be interrupted/discontinued at the discretion of the investigator. The patient’s medication will be reviewed daily to evaluate DDIs including drugs prolonging the QTc interval according to what is listed in the protocol (see Additional file 1)

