### Data collection and management

#### Plans for assessment and collection of outcomes {18a}

##### Collection of baseline parameters

After consent has been given, the following data are obtained retrospectively from the patient’s file: demographics, medical history, parameters and values of assessments from the moment of admission (vital signs, do not resuscitate (DNR)-code, clinical assessments, history taking, respiratory support, ECG, lab values). These should be obtained as part of routine clinical care. When study-related procedures impose an additional burden on the clinical care of patients, they can be waived. The assessment closest in time or most relevant to the situation at baseline will then be used instead.

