### Statistical methods

#### Statistical methods for primary and secondary outcomes {20a}

Hereby provided is a summary of the most important statistical analyses. Further details will be outlined in the SAP that will be finalized before database lock.

This open-label controlled randomized trial tests a superiority hypothesis with a two-sided type I error rate of 0.05. Secondary hypotheses of this exploratory study will be tested in a non-hierarchical way. These will be described according to the appropriate summary statistics (e.g., proportions for categorical data, means with 95% confidence intervals for continuous data, median for time-to-event data).

The primary outcome is based on an ordinal severity scale with 7 categories. This scale has been proposed by the WHO for COVID-19-related research and has been previously used in trials of patients with influenza. Previously reported studies and ongoing studies record the same primary outcome, which allows cross-study data pooling. The primary endpoint will be analyzed by means of competing risk analyses whereby death without any improvement will be considered as a competing risk. Event rates will be estimated using cumulative incidence functions (CIF). Median times to improvement will be calculated by the treatment group. The effect of treatment will be assessed by performing a Fine and Gray competing risk regression model that includes the baseline value on day 0 as a covariate and randomized treatment as a factor. From the Fine and Gray model, the subdistribution hazard ratio and associated 95% confidence interval will be estimated.

Secondary endpoints will be analyzed as follows:

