Cumulative clinical status up to day 15 will be analyzed using a general linear model adjusted for clinical status on day 0. The treatment effect will be estimated by the difference of mean values between the groups.Cumulative clinical status recorded daily during the hospital stay and on days 15 and 19 will be analyzed by means of a proportional odds logistic regression model, adjusted for clinical status on day 0. The treatment effect will be estimated by the common odds ratio.All-cause mortality rates will be estimated by treatment group using the Kaplan-Meier method. The resulting Kaplan-Meier curves will be compared using a log-rank test. The treatment effect will be estimated by the hazard ratio using a Cox regression.Other time-to-event parameters with competing risk: event rates will be estimated using cumulative incidence functions (CIF), and the resulting CIF curves will be compared using Gray’s test. The treatment effect will be estimated by the subdistribution hazard ratio.Duration of hospital and ICU stay: both parameters will be analyzed as time-to-event parameters with competing risk, whereby the event of interest is discharge from hospital/ICU and the competing risk is hospital/ICU death.Continuous normally distributed variables (e.g., QTc) will be analyzed using a 2-sample *t* test. Treatment effects will be estimated by the difference in mean values between the groups. If applicable, changes from baseline will be calculated. Comparisons between treatment groups will be done by performing an analysis of covariance (ANCOVA) on the post-baseline value, using the baseline value as a covariate.Continuous non-normally distributed variables (clinical status, NEWS score, duration of supplemental oxygen, duration of mechanical ventilation) will be analyzed using a Wilcoxon rank-sum test. Change in ordinal scale at specific time points will be compared using Wilcoxon rank-sum tests.

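### NEWS is compared by an unadjusted Wilcoxon test although its baseline is collected, which gives up power and leaves no place for the promised period and center adjustments

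*Protocol article*

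**What the plan says.** Section {20a} of the protocol sorts continuous secondary variables by the shape of their distribution.

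- Judged normal: "Continuous normally distributed variables (e.g., QTc) will be analyzed using a 2-sample" t test. Treatment comparisons then come from "performing an analysis of covariance (ANCOVA) on the post-baseline value, using the baseline value as a covariate".
- Judged non-normal: "NEWS score, duration of supplemental oxygen, duration of mechanical ventilation) will be analyzed using a Wilcoxon rank-sum test". This item names no covariate. It also lists clinical status and adds a rank-sum test on change for the ordinal scale, but states no such test for NEWS.

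Elsewhere the section does use a day-0 value for outcomes that are not normal. Ordinal clinical status gets a "proportional odds logistic regression model, adjusted for clinical status on day 0". The primary Fine and Gray model "includes the baseline value on day 0 as a covariate and randomized treatment as a factor". The linear model for cumulative status is also adjusted for day 0.

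NEWS is a declared secondary outcome, assessed daily in hospital and on days 15 and 29. The daily-assessment list identifies the recorded vital signs as the NEWS items. The participant timeline marks "Vital signs including SpO2" at both screening and baseline, and the section on baseline parameters has the team extract "parameters and values of assessments from the moment of admission (vital signs" onward. The laboratory row, "CRP, hematology, chemistry, kidney and liver test", is marked at screening and is at the clinician's discretion from baseline until discharge.

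Two further commitments bear on the test. The sample size section says that every analysis will be corrected for recruitment period. Section {20a} says that differences between centers and changes in standard of care will be adjusted for.

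**The concern.** Non-normality is a reason to avoid a normal-theory model. It is not a reason to drop the baseline. Patients enter this trial anywhere from the ordinary ward to the ICU, so part of the spread in follow-up NEWS can be expected to reflect where each patient started. Randomization is blocked within center only, so it does not balance severity by design. A test that ignores baseline NEWS leaves that spread in the error term. At stake is the precision of one named secondary efficacy outcome, and whether its analysis can honor the adjustments that the protocol promises for all analyses.

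**Working it through.** **1. Where the plan uses a baseline**

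| Outcome | Stated analysis | Baseline used? |
|---|---|---|
| Primary time-to-event | Fine and Gray | Yes, day-0 status |
| Ordinal clinical status | Proportional odds (also rank-sum) | Yes, in the model |
| Cumulative status to day 15 | General linear model | Yes, day-0 status |
| Continuous, judged normal (e.g., QTc) | t test, ANCOVA | Yes, in the ANCOVA |
| NEWS | Wilcoxon rank-sum | No |

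**2. Sample size for the check**

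The plan states no power for NEWS, so I take its evaluable number for the primary outcome. With the Schoenfeld formula at 2:1, HR = ln(1−0.575)/ln(1−0.40) = 1.675. Events = (1.960+0.842)²/[(2/9)(ln 1.675)²] = 132.7, rounded up to 133. The mean event rate is (0.40+2×0.575)/3 = 0.517, and 133/0.517 = 257.4 (stated: 258). The same method gives 354.0 (stated: 354) for a 15% difference and 195.0 (stated: 196) for 20%. I therefore use 172 vs 86 patients.

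**3. Normal-theory size of the loss**

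Let r be the correlation between baseline and follow-up. The documents give none, so r from 0.3 to 0.7 is an assumption. Adjustment multiplies the residual variance by 1−r². The standardized difference with 80% unadjusted power is d = 2.802×√(1/86+1/172) = 2.802×0.1321 = 0.370. Adjusted power is Φ(2.802/√(1−r²) − 1.960).

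| r | 1−r² | Adjusted power | N for 80% power, 258×(1−r²) |
|---|---|---|---|
| 0.3 | 0.91 | 83.6% | 235 |
| 0.5 | 0.75 | 89.9% | 194 |
| 0.7 | 0.51 | 97.5% | 132 |

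**4. Simulation with rank methods**

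First simulation: a skewed integer score from 0 to 20, a shift of 0.37 SD on the underlying normal scale where r is also defined, and 3,000 trials per setting.

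| r | Wilcoxon | Rank ANCOVA | Gain (points) |
|---|---|---|---|
| 0.3 | 76.2% | 79.4% | 3.2 |
| 0.5 | 75.4% | 84.7% | 9.3 |
| 0.7 | 77.0% | 94.9% | 17.9 |

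Second simulation: a rounded normal score, a shift of 0.33 SD, and 2,500 trials per setting. Wilcoxon power was 67%. Rank ANCOVA gave 70% (r=0.3), 78% (r=0.5), 84% (r=0.6) and 90% (r=0.7), which are gains of 3, 11, 17 and 23 points. Together, the loss is about 3 points at r=0.3 and about 20 (18 to 23) at r=0.7.

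**5. Validity**

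With no treatment effect, rejection rates were 4.6–5.1% for both methods in the second simulation and about 4–5% in the first. In the trials where the arms differ at baseline by more than 1.5 standard errors (about 13% of trials), the unadjusted test rejects about 11% (r=0.5) to 17% (r=0.6) of the time in simulation. By large-sample theory these rates are 13% and 17%, and the remaining 87% of trials reject about 3.7% and 3.2%. The averages are 0.13×0.13+0.87×0.037 = 4.9% and 0.13×0.17+0.87×0.032 = 5.0%. The overall error rate is as planned.

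**6. What the named test can carry**

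A two-sample rank-sum test takes no covariates. A stratified version could take period and center as strata, but that is not the test named, and it would not take baseline NEWS as a score. Rank ANCOVA or a proportional-odds model takes all three.

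**The case against.** The strongest reply is that the named test is valid, and that NEWS is one of many secondary outcomes in a study the protocol itself calls exploratory. NEWS has no sample-size target, and a related severity measure, clinical status, already has adjusted analyses. All of that stands, and it limits the weight of the point.

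The power figures also need care. They assume complete NEWS in 258 patients, but vital signs are scheduled only until discharge. Days 15 and 29 are telephone evaluations in the timeline, where most NEWS items cannot readily be measured, and patients who have died have none. On later days the scores come mainly from patients still in hospital, so the figures do not describe those analyses. Baseline values are extracted retrospectively, and burdensome procedures may be waived with the nearest assessment substituted, so baseline NEWS may not be complete either. At r=0.3 the gain is only about 3 points.

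Four stronger readings are tempting, and the documents do not support them.

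- That the whole plan uses baselines only for normal variables. The primary model and both clinical-status models contradict this; the pattern holds only among the continuous secondary variables.
- That the test is biased or has inflated error. The 11–17% rates hold only given a chance baseline imbalance; over all trials the rate is about 5%.
- That laboratory values are assigned to the Wilcoxon test. None is named there. One would fall there only if judged non-normal, and the SAP may specify a transformation.
- That no effect size would be reported for NEWS. The section provides in general for descriptive means with 95% confidence intervals.

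The article is a summary and leaves detail to the SAP. For NEWS, however, it states the test outright, so this is a choice made and not a detail left open.

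**Conclusion.** The point holds as a loss of efficiency in one named secondary outcome. The protocol sets an unadjusted rank-sum test for NEWS while collecting the baseline that would sharpen it, and while adjusting a comparable ordinal outcome for day 0. With 172 vs 86 patients, complete data, and an assumed r of 0.3 to 0.7, the cost is about 3 to 20 points of power. Beyond the early hospital days the size is uncertain. The named test also cannot carry the period and center adjustments promised elsewhere in the protocol, and that mismatch does not depend on any assumed correlation. Neither the primary analysis nor the validity of the NEWS test is in question. The change is worth making because the SAP is still to be finalized before database lock.

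**What to change.** In section {20a}, or in the SAP before lock, replace the Wilcoxon test for NEWS at each analysed in-hospital day. Use either rank ANCOVA or a proportional-odds model on the post-baseline score, with day-0 NEWS as covariate plus the promised period and center terms. If the proportional-odds model is chosen, report the common odds ratio with its 95% confidence interval. If any laboratory value is judged non-normal, keep its available baseline as covariate in the same way, by ANCOVA on the log scale or by rank ANCOVA.

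The cost is a sentence or two of text, with no new data, visits or patients. The downside is a model assumption that the plain rank-sum test does not make: proportional odds where that model is used, and a form for the baseline term. The change does not address missing NEWS after discharge or death.

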##### Visit at days 15 (± 2) and 29 (± 3)

These visits can be phone visits when patients are no longer hospitalized or when safety issues do not permit physical contact. Primary and secondary outcomes are systematically assessed with standardized worksheets provided by the sponsor (complete set of worksheets can be provided on request).

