#### Methods in analysis to handle protocol non-adherence and any statistical methods to handle missing data {20c}

All efficacy analyses are based on the intention-to-treat principle and are performed on the Full Analysis Set (FAS). The FAS includes all randomized patients according to their randomized treatment. However, COVID-negative patients who were mistakenly randomized will be omitted from the FAS. Missing clinical status data will be accounted for by multiple imputation methodology using a total of 100 imputations [22].

Patients from the FAS with major protocol violations will be excluded from the Per Protocol Set (PPS). The PSS will be reviewed and finalized at the Blind Review Meeting just prior to database lock.

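### Oxygen and ventilation durations go to a plain Wilcoxon test with no rule for death, although the same section treats death as a competing risk for hospital and ICU stay

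*Protocol article*

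**What the plan says.** Section {20a} of the protocol article names a method for each type of secondary outcome. For the two support durations, grouped with clinical status and NEWS as continuous variables without a normal distribution, it reads: "duration of supplemental oxygen, duration of mechanical ventilation) will be analyzed using a Wilcoxon rank-sum test". No value or rank is given to a patient who dies while on support.

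The neighbouring durations are handled differently: "Duration of hospital and ICU stay: both parameters will be analyzed as time-to-event parameters with competing risk", where "the event of interest is discharge from hospital/ICU and the competing risk is hospital/ICU death". For the primary endpoint, too, "death without any improvement will be considered as a competing risk". There is a general line for other time-to-event parameters with competing risk, but the oxygen and ventilation durations are listed under the Wilcoxon test instead.

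The missing-data rule in {20c} does not fill the gap, because it covers clinical status only: "Missing clinical status data will be accounted for by multiple imputation methodology using a total of 100 imputations".

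NEWS is a secondary outcome daily in hospital and on days 15 and 29. The participant timeline {13} schedules vital signs until discharge and shows a telephone evaluation on days 15 and 29. The section on those visits adds: "These visits can be phone visits when patients are no longer hospitalized".

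**The concern.** Days of oxygen or ventilation can end in two opposite ways: the patient is weaned, or the patient dies. A rank-sum test on the number of days does not distinguish them. A patient who dies on a ventilator on day 3 ranks ahead of one weaned alive on day 10. If mortality is the same in both arms this costs interpretability but does not distort the type I error. If mortality differs, the test answers a mixture of two questions, and its direction depends on when the deaths occur.

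This matters here because the protocol itself raises possible cardiac harm, notably in combination with hydroxychloroquine (Sample size {14}). An excess of deaths on azithromycin is therefore a scenario the sponsor considers. In that scenario a shorter duration of support could be read as benefit.

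For NEWS the mechanism is different. On days 15 and 29 the score will come largely from survivors still in hospital, a group selected after randomisation. An arm that discharges its recovering patients sooner removes them from its own comparison.

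**Working it through.** The plan gives no mortality, time of death or duration of support, so there is no figure of its own to reproduce on this point. From the plan: 2:1 allocation ({14}) and a two-sided 5% level ({20a}). Everything else below is assumed. Weaning is identical in both arms throughout, so any difference is produced by death.

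**Step 1: raw medians.** Assume exponential weaning with median 10 days, hazard w = ln 2 / 10. If a share d dies on support, the death hazard is w·d/(1−d) and the total hazard is w/(1−d). The median raw duration is then 10·(1−d): 8.2 days at 18% deaths, 7.7 at 23%, 6.8 at 32% and 5.9 at 41%.

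**Step 2: how often the test favours the arm with more deaths.** Take 120 supported patients, 40 and 80, with more deaths in the larger arm. The probability that a patient in that arm has the shorter duration is θ = (1−d_low) / [(1−d_low) + (1−d_high)]. The null standard error of the rank-sum estimate of θ is √[(40+80+1)/(12·40·80)] = 0.0561. The wrong-direction rate is about P(Z > 1.96 − (θ−0.5)/0.0561).

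| Deaths on support | θ | (θ−0.5)/0.0561 | Formula | Simulation |
|---|---|---|---|---|
| 18% vs 18% | 0.500 | 0 | 2.5% | about 2% |
| 18% vs 23% | 0.82/1.59 = 0.516 | 0.28 | 4.6% | about 4% |
| 18% vs 32% | 0.82/1.50 = 0.547 | 0.83 | 13% | 12% |
| 18% vs 41% | 0.82/1.41 = 0.582 | 1.45 | 31% | 31% |

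With 200 supported patients, 18% vs 41% gives 48%. Capping follow-up at 29 days barely changes these rates. Exchanging which arm has more deaths gives similar ones (12% and 31% for the last two rows).

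**Step 3: dependence on timing of death.** In the exponential model deaths cluster early. To vary this, take lognormal weaning (median 7 or 12 days, log-SD 0.8, capped at 29 days), 60 vs 120 supported patients and 18% vs 32% deaths. Patients who die stay on support until death.

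- Deaths on days 1 to 8: wrong-direction significant result in 8 to 21% of trials.
- Deaths spread over days 1 to 29: 0.5 to 2%.
- Deaths on days 8 to 29: 0.2 to 0.7%. The arm with more deaths instead shows significantly longer support in 6 to 20%.

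The last two results depend on patients staying on support until death. When I let patients be weaned before dying, the rate for spread or late deaths was about 3 to 6%, slightly above nominal.

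**Step 4: effect of a death rule.** In a separate run (86 vs 172 patients, deaths on days 1 to 8), the raw test went the wrong way in 10 to 17% of trials for a 10-point mortality excess and 28 to 52% for a 20-point excess. With deaths ranked worst and the same Wilcoxon test, this fell to at most 0.2%.

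**Step 5: NEWS.** The daily-assessment section builds NEWS from blood pressure, heart rate, temperature, SpO2, respiratory rate, oxygen supplement and AVPU. The timeline stops vital signs at discharge and offers a telephone evaluation on days 15 and 29. Most of these components are not obtained in a telephone call, and a patient who has died has no score. No size is given, because the documents do not state what share is still in hospital on those days.

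**The case against.** The strongest reply is that {20a} calls itself a summary and defers detail to an SAP that is not shown. It names a test but does not define the duration variable, and scoring of deaths is ordinary SAP content. The Wilcoxon test is also compatible with a sound analysis: support-free days with death ranked worst is usually compared by exactly that test. This stands in part. A reader might infer that the plan states that deaths are scored as short durations; it does not. What remains is that the article assigns these two durations by name to a test for plain continuous variables, while giving the other two a competing-risk analysis. That is an inconsistent choice already made, not a detail left open.

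A second reply concerns size. A reader might infer that the arm with more deaths will generally look better. The documents do not support that. They contain no mortality or timing figures, the effect is small for a 5-point gap, and with late deaths on support it disappears or reverses. This stands, and the range in the working reflects it.

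Third, a reader might infer that NEWS on days 15 and 29 exists only for inpatients. Telephone visits are permitted, not required, so the supportable statement is that the scores will come largely from inpatients. Clinical status, listed in the same sentence, is not affected by this gap, because death is a category of its scale.

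Finally, mortality is reported separately, so a mortality difference would be visible beside these durations. That limits the harm but does not make the duration comparison interpretable.

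**Conclusion.** The point holds as an inconsistency with a real but conditional consequence. Two of the four durations have death handled as a competing risk and two do not. For the latter, the comparison mixes survival with weaning whenever mortality differs.

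Under the assumptions shown, the wrong-direction rate runs from about 4% (18% vs 23% deaths) through 8 to 21% (18% vs 32%, early deaths) to 31% (18% vs 41%), against a nominal 2.5%. For 18% vs 32% it is at or below nominal if deaths on support are spread over 29 days or come late and patients remain on support until death. Neither the sign nor the size can be fixed from the documents.

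The NEWS point is secondary and one of selection, not of death mimicking less support. All of these are exploratory secondary outcomes. The primary endpoint already treats death as a competing risk, and neither its analysis nor the sample size changes.

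**What to change.** Replace the Wilcoxon entry for the two support durations with one of the following, and state which is the main analysis:

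- Among patients on support, analyse time to end of support alive, with death as the competing event, using the cumulative incidence functions, Gray's test and subdistribution hazard ratio already planned. Defining the group by support at baseline keeps it fixed before randomisation. This analysis is not defined for patients never on support.
- In all randomised patients, compare support-free days to day 29, with death ranked worst and no support needed ranked best, keeping the Wilcoxon test. Label it as a composite of survival and support, because a mortality difference will drive it.

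State also whether oxygen continued after discharge counts towards the duration.

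For NEWS on days 15 and 29, either report it descriptively among those with a score, giving the numbers dead and discharged in each arm, or rank death worst and discharge best. The second option largely repeats the ordinal scale.

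The cost is a few sentences in the SAP, which is to be finalised before database lock, and reuse of planned programs. No new data are needed.
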